#### Secondary Objective

Our secondary objective is to collect preliminary data on efficacy and toxicity as exploratory outcomes for this pilot. Specifically, we will evaluate the incidence of clinically progressive disease, changes in tumour marker levels, and incidence of clinically relevant toxicities. As an exploratory outcome, we will explore the utility of tumour markers such as CEA, CA19-9 and ctDNA in higher-frequency serial measurements with modulated doses. We will also explore ctDNA as an input for CURATE.AI to generate dose recommendations, however we will not use this analysis to prospectively guide dosing. We provide further details in our outcome measures below.

### Study Timeline and Investigations

The study investigations schedule is summarised in Figure 2. For each participant, we will perform regular reviews of medical history, physical examination including performance status and vital signs, and documentation of adverse events and concomitant medications as per standard-of-care. We will also perform standard-of-care investigations at regular intervals, such as but not limited to: haematology, serum chemistries, traditional tumour markers (e.g., CEA or CA19-9) and computed tomography (CT) scans. We will conduct these investigations following standard-of-care institutional laboratory techniques and radiographic protocols.

**Figure 2 F2:**

Overall trial schedule for 3 weeks long cycles. BI: Baseline investigations as per standard-of-care, including collection of demographics, medical/treatment history, vital signs, and conducting complete physical examination including performance status evaluation, blood tests [haematology, serum chemistries, tumour marker(s)] and imaging as clinically required. BD: Mandatory blood draws done every 3 weeks for the measurement of tumour marker(s) between Days 17–20 of each cycle, alongside serum chemistries and haematology as per standard-of-care. BD*: Additional blood draws for measurements of tumour markers(s), done once weekly (once between Days 4–7, and another between Days 11–14) performed solely for the purposes of the trial, and are necessary for cycles 1–2 of chemotherapy. Additional blood draws in subsequent cycles will be limited to one draw, if at all. CT*: Computed tomography scans performed approximately every two or three cycles as per standard-of-care. End of study: upon completion of all chemotherapy cycles, or at 12 months, whichever is earlier for each participant.

There are two main deviations from standard-of-care in our study investigations. Firstly, we will perform the same blood draws and disease assessments but at more frequent intervals than standard-of-care (weekly compared to 3-weekly), to investigate temporal variations in tumour marker level. However, we will limit this increased frequency to the first two chemotherapy cycles and a maximum of one additional blood test per subsequent cycles. Secondly, we may measure participants' serum ctDNA at a similar or lower frequency as the above blood draws. ctDNA measurements, if performeed, will be regularly spaced, with ~4 measurements per patient over four cycles. ctDNA is not routinely measured in standard-of-care.

We may perform other blood tests as per the clinical investigator's judgement. The clinical investigator will perform history and physical examination, as well as review of the adverse events prior to the start of every subsequent cycle of chemotherapy, as per local institution standards. We will enrol participants for the entire duration of their treatment with the selected regimens, up to a maximum of 12 months per participant. We will document the above findings for each participant.

### Sample Size

Since this is a pilot clinical trial with no precedent data, we did not perform an upfront formal sample size calculation. We intend to first recruit 10 patients and perform an interim analysis using the data generated from these participants, which will include formal power and statistical sample size calculations. Based on these outcomes, we will consider cohort expansion or an RCT.

### Data Collection, Management, and Analysis

#### Primary Outcome Measure

The primary outcome measure (Table 1) is the percentage of participants in whom we successfully apply a CURATE.AI profile. This is the main outcome which we will use to judge the technical feasibility of a future RCT and corresponds to the first of our primary objectives. A decision on whether we “successfully apply” the CURATE.AI profile requires expert judgement and cannot be made based on a purely numerical process therefore the statistical analyses will be viewed within the broader framework of clinical relevance. An expert panel, comprising physicians and researchers not involved in the trial, will consider the following factors with careful regard for the individual circumstances of each participant: (1) based on clinical experience, judgement and established indicators, the error/variance analyzed with descriptive statistics of numerical performance measures [i.e., mean absolute error, error distribution and bias (the frequency and extent of under- and overpredicting)] is acceptable to guide clinical decisions; (2) profile can be generated sufficiently early for the participant to potentially benefit; (3) dose-dependent relationship is observed; (4) profile is actionable (i.e., fulfils the clinical investigator's pre-specified safety requirements); (5) systemic changes in the participant which require profile recalibration are rare or readily assimilated into the CURATE.AI algorithm. This is the main outcome which we will use to judge the technical feasibility of the RCT. As per the CONSORT extension statement for pilot clinical trials, we are using “the traffic light system” to define progression criteria for the RCT (33).

#### Secondary and Exploratory Outcome Measures

The secondary outcome measures (Table 1) focus on both technical and logistical feasibility, which constitute our primary objectives. Secondary outcomes include: (1) patient adherence to the prescribed dose; (2) timeliness of CURATE.AI recommendations to the physician in time for the next chemotherapy cycle, across all participants and cycles; (3) physician adherence to CURATE.AI recommended doses; (4) clinically significant dose changes where a participant's CURATE.AI-guided cumulative dose is ≥10% different from the projected standard-of-care cumulative dose.

Exploratory outcome measures (Table 1) mainly relate to efficacy and toxicity, which constitute our secondary objectives. Exploratory outcomes relating to efficacy include: (1) percentage of trial participants with clinical progressive disease defined as the clinical investigator deeming that the patient will not benefit any further from the chemotherapy regimen and considering stopping it, at the time of the first radiological assessment performed as per standard-of-care; as well as (2) temporal variation and (3) maximal reduction in tumour marker level from trial initiation to conclusion. We will also measure clinically relevant toxicities of grades 3–4 as an exploratory outcome, using the Common Terminology Criteria for Adverse Events (CTCAE) version 4.0. Other exploratory outcomes include data collection and exploratory analysis of CEA, CA19-9 and/or other traditional tumour markers in higher frequency serial measurements after modulated dosing in relation to standard frequency readings and other efficacy measures, e.g., RECIST criteria. Finally, we will perform data collection and exploratory analysis of ctDNA as a tumour marker in serial measurements at given clinical context and after modulated dosing, as well as a potential input for CURATE.AI. However, we will not use the analysis of ctDNA to prospectively guide drug dosing in this pilot clinical trial.

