## Abstract

**Introduction:** Oncologists have traditionally administered the maximum tolerated doses of drugs in chemotherapy. However, these toxicity-guided doses may lead to suboptimal efficacy. CURATE.AI is an indication-agnostic, mechanism-independent and efficacy-driven personalised dosing platform that may offer a more optimal solution. While CURATE.AI has already been applied in a variety of clinical settings, there are no prior randomised controlled trials (RCTs) on CURATE.AI-guided chemotherapy dosing for solid tumours. Therefore, we aim to assess the technical and logistical feasibility of a future RCT for CURATE.AI-guided solid tumour chemotherapy dosing. We will also collect exploratory data on efficacy and toxicity, which will inform RCT power calculations.

**Methods and analysis:** This is an open-label, single-arm, two-centre, prospective pilot clinical trial, recruiting adults with metastatic solid tumours and raised baseline tumour marker levels who are planned for palliative-intent, capecitabine-based chemotherapy. As CURATE.AI is a small data platform, it will guide drug dosing for each participant based only on their own tumour marker levels and drug doses as input data. The primary outcome is the proportion of participants in whom CURATE.AI is successfully applied to provide efficacy-driven personalised dosing, as judged based on predefined considerations. Secondary outcomes include the timeliness of dose recommendations, participant and physician adherence to CURATE.AI-recommended doses, and the proportion of clinically significant dose changes. We aim to initially enrol 10 participants from two hospitals in Singapore, perform an interim analysis, and consider either cohort expansion or an RCT. Recruitment began in August 2020. This pilot clinical trial will provide key data for a future RCT of CURATE.AI-guided personalised dosing for precision oncology.

**Ethics and dissemination:** The National Healthcare Group (NHG) Domain Specific Review Board has granted ethical approval for this study (DSRB 2020/00334). We will distribute our findings at scientific conferences and publish them in peer-reviewed journals.

**Trial registration number:** NCT04522284

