Predicting the optimal dose at a single point in time is only part of the challenge. The optimal dose evolves throughout the course of treatment, with the participant's response to therapy evolving due to environmental, physiologic and disease changes, including drug resistance (7). Here, CURATE.AI's ability to continually recalibrate personalised profiles allows for dynamic dose optimisation throughout treatment (23, 24). To maximise CURATE.AI's therapeutic potential, it is thus paramount to utilize a phenotypic response biomarker that can be quantified frequently. Though the gold standard for monitoring treatment response in solid tumours is the Response Evaluation Criteria in Solid Tumours (RECIST), these radiological assessments are performed at infrequent intervals after a few chemotherapy cycles, and may not reflect the entire tumour burden in situations such as widespread metastases or central necrosis (26). Blood-based tumour markers, such as carcinoembryonic antigen (CEA) and carbohydrate antigen 19-9 (CA19-9) (27–29), can be measured more frequently. However, these traditional blood biomarkers have limited sensitivity and specificity in reflecting tumour response, especially among patients whose baseline biomarker levels are in the normal range (30). Recent advances in genomic sequencing have revealed plasma circulating tumour DNA (ctDNA) as a novel biomarker of tumour burden (31). ctDNA are DNA fragments released by tumour cells, *via* apoptosis, necrosis or active secretion. These fragments contain both genetic information (such as point mutation, copy number variation) and epigenetic information (such as DNA methylation). Quantitative changes in ctDNA have been shown to be ultra-sensitive in detecting both macroscopic and microscopic tumour load (32), including in patients without raised traditional tumour markers at baseline. Therefore, serial ctDNA measurements may be more reflective of the evolving tumour response and thus appropriate for CURATE.AI.

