*percentage of participants in whom the CURATE.AI-guided cumulative dose is substantially (≥10%) different from the projected standard-of-care cumulative dose, which is defined as the maximum dose of capecitabine (1,000 mg/m^2^ twice daily for XELOX and XELIRI regimen, 1,250 mg/m^2^ twice daily for single agent capecitabine regimen) multiplied by the number of completed chemotherapy cycles.*

f
*defined as the clinical investigator deeming that the patient will not benefit any further from the chemotherapy regimen and considering stopping it, at the time of the first radiological assessment performed as per standard-of-care.*

g
*of grades 3–4 based on Common Terminology Criteria for Adverse Events (CTCAE) version 4.0.*

*ctDNA, circulating tumour DNA*.

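### Clinical progressive disease is scored only by investigator judgement at the first routine scan, so progression or disease death before that scan is not counted and the rate may not transfer to a RECIST endpoint

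*Protocol article*

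**What the plan says.** Under Secondary and Exploratory Outcome Measures, clinical progressive disease is the first efficacy outcome listed and is reported as a percentage. It is "defined as the clinical investigator deeming that the patient will not benefit any further from the chemotherapy regimen and considering stopping it". The judgement is made "at the time of the first radiological assessment performed as per standard-of-care". Table 1, footnote f, gives the same definition with the same timing. The scan fixes when the judgement is made; no imaging finding forms part of it.

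The Abstract describes the design: "This is an open-label, single-arm, two-centre, prospective pilot clinical trial". Figure 2 places CT about every two or three cycles. RECIST enters the outcome list only through the higher-frequency marker analysis, where marker readings are examined "in relation to standard frequency readings and other efficacy measures, e.g., RECIST criteria".

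Under Study Setting and Participant Recruitment, participants who do not complete two uninterrupted cycles are unevaluable for the primary outcome and are replaced. Adverse events are the only follow-up promised for them there. The Abstract, the end of the Introduction and the Conclusions say that the exploratory efficacy and toxicity data will serve power or sample size calculations for a future RCT.

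**The concern.** Two features of the definition reduce the value of the percentage it produces.

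The first is timing. An outcome judged at one scan has no place for a participant whose disease has already ended treatment, or life, before that scan. These are the clearest failures, and leaving them out can only lower the percentage or leave it unchanged.

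The second is content. Whether an investigator is considering stopping depends on more than tumour growth. A participant with radiological progression whose treatment continues need not be an event, and one with stable scans can be. If the later trial uses a RECIST-based endpoint, the pilot rate estimates something else.

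At stake is the efficacy information passed to the design of the RCT. The pilot's own green, yellow and red criteria do not depend on this outcome.

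**Working it through.** The plan gives no event rate or target for this outcome, so there is no figure to reproduce. The check covers timing, counting and a comparison of the relevant sections.

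**When the first scan falls.** Inputs: 3-week cycles (Choice of Chemotherapy Regimens) and CT about every two or three cycles (Figure 2).
- 2 cycles × 3 weeks = 6 weeks (day 42)
- 3 cycles × 3 weeks = 9 weeks (day 63)

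The period in which an event can be missed is therefore about 6 to 9 weeks. This is inferred from an approximate interval; no fixed date for the first scan is given.

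**Who can be missed.** A participant who fails during the first two cycles is normally unevaluable for the primary outcome and is replaced. A participant who completes two cycles (6 weeks) and then fails before a scan at week 9 stays among the 10 evaluable participants but has no qualifying judgement. Both routes are open.

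**Effect of one missed event.** Let x be the number of events scored at the scan among the evaluable participants. The article does not say which denominator applies to such a participant, so each possibility is shown.

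| Handling of one early failure | Reported | With the event counted among all enrolled | Understatement |
|---|---|---|---|
| Among the 10, kept in the denominator as a non-event | x/10 | (x+1)/10 | 1/10 = 10.0 points |
| Among the 10, dropped for want of an assessment | x/9 | (x+1)/10 | (9−x)/90: 10.0 points at x = 0, 0 at x = 9 |
| Replaced, but kept in the denominator as a non-event | x/11 | (x+1)/11 | 1/11 = 9.1 points |
| Replaced and left out | x/10 | (x+1)/11 | (10−x)/110: 9.1 points at x = 0, 0 at x = 10 |

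The understatement is never negative. Its size for this trial is unknown, because the document gives no rate of early failure.

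**Transfer to RECIST.** The definition needs two things, a view that there is no further benefit and consideration of stopping. Neither requires a measured change on the scan. With 10 participants, each one whom the two definitions classify differently moves the percentage by 1/10 = 10 points. No discordance rate is given, so the total shift cannot be estimated.

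**The case against.** The strongest case against is that this is a preference about an exploratory measure. The outcome is labelled clinical, is defined identically in both places and is never presented as RECIST progression. The Introduction calls RECIST the gold standard, but the same sentence says that radiological assessment is infrequent and "may not reflect the entire tumour burden in situations such as widespread metastases or central necrosis". Choosing a clinical judgement does not contradict that section. Table 1 sets no threshold for the outcome, and Statistical Analysis rules out statistical analysis of it. With one arm, open-label assessment cannot bias a comparison between arms. All of this stands. It keeps the point minor and argues against replacing the outcome outright.

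A reader might go further and infer that the marker CURATE.AI optimises drives this outcome. The document does not support that. A profile needs at least three data pairs, one per cycle, so 3 × 3 = 9 weeks. Efficacy-driven doses then begin in cycle 4 at the earliest, and the first scan normally falls while doses are still for calibration. Nothing stops the investigator from weighing marker values, but no section says that they decide the judgement.

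A reader might also infer that a planned comparison of markers with clinical progression is circular. No such comparison is specified. The only comparator named as an example is RECIST.

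It can also be said that a sensible reader would count an earlier death from disease as progression, and that the full protocol or analysis plan may say so. That is possible. But the article states the timing explicitly and twice, and the literal wording excludes the case. The replacement rule adds to the loss, so rewording footnote f without naming the denominator would not settle it.

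**Conclusion.** The concern holds in a limited form and is minor. As written, the outcome does not count progression or disease death before about weeks 6 to 9. One such case lowers the percentage by up to 10 points with 10 participants. The rate also lacks a radiological criterion, so it may not carry over to a RECIST-based endpoint in the future RCT.

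This rests on three assumptions: that the timing phrase is taken literally, that the first scan follows the two-to-three-cycle interval, and that the RCT might use a RECIST-based endpoint, which the document does not state. The pilot's feasibility decision is unaffected.

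**What to change.** In Secondary and Exploratory Outcome Measures and in Table 1, footnote f:

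1. Change the timing to at or before the first radiological assessment.
2. State that documented progression or death from disease before that scan counts as an event.
3. State that the denominator is all enrolled participants, including those replaced as unevaluable for the primary outcome.
4. Report RECIST progressive disease on the same routine CT as a separate item beside the investigator's judgement, which is kept.

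The cost is small. The scans are already part of standard care and RECIST is already named in the marker analysis, so the extra work is the RECIST readings and recording disease outcome for replaced participants. Participants without measurable disease will need a non-target rule. The change concerns outcome counting only and alters no treatment decision.

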### Study Setting and Participant Recruitment

We will recruit participants at two centres: National University Hospital (NUH) and Ng Teng Fong General Hospital (NTFGH), which both belong to the National University Health System (NUHS), Singapore. Clinical investigators will recruit patients from outpatient clinics during routine clinical reviews, weekly trial meetings or multidisciplinary tumour boards. As this is a pilot clinical trial with no precedent data, we intend to first recruit 10 patients and perform an interim analysis, which will include formal power and statistical sample size calculations. Based on these outcomes, we will consider an RCT, or an amendment of this study protocol to expand the current cohort or to include further cohorts of patients with a wider range of chemotherapy regimens or tumour markers. We will consider participants to be evaluable for the primary outcome measures only if participants are able to complete the first two cycles of chemotherapy in an uninterrupted manner. We will replace any unevaluable participants with new participants, though we will continue to monitor and report any adverse events in the unevaluable participants. We will consider replacing participants who withdraw from the study (see Supplementary Text) with new participants if we could not collect sufficient data for primary outcome assessment.

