#### CURATE.AI Efficacy-Driven Dose Recommendations

After the CURATE.AI profile is generated, we will check it for actionability, defined as the ability to recommend an optimum dose within the safety requirements pre-specified by the clinical investigator (Figure 1, Step 4). For participants with actionable profiles, CURATE.AI will recommend therapeutic-intent, efficacy-driven doses to the clinical investigator (Figure 1, Step 5). Any dose recommended by CURATE.AI will always be within the safe dose range pre-specified by the clinical investigator. If the dose-dependent relationship is maintained, CURATE.AI will continue to use the existing profile to provide dynamic dose recommendations before every subsequent cycle (Figure 1, Step 6.1). This continues until the end of the participant's involvement in the study (Figure 1, Step 7), which is when the clinical investigator decides to cease/change the chemotherapy regimen, or until 12 months, whichever is earlier. If the dose-dependent relationship is not maintained but we do not suspect systemic changes in the participant (Figure 1, Step 6.2), CURATE.AI will obtain a new data pair in the next cycle based on the existing profile. If the dose-dependent relationship is not maintained and we suspect systemic changes in the participant at any point during the trial, such as but not limited to the introduction of haemodialysis or drugs with known interactions with the treatment, CURATE.AI may recalibrate the personalised profile (Figure 1, Step 6.3) to generate a new profile for the participant. CURATE.AI will select recalibration doses on the basis of previous correlations.

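### Clinical progressive disease is tied to the first scan, so participants who die of disease or stop for clinical deterioration before it cannot meet the definition, and the rate is biased downward for them

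*Protocol article*

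**What the plan says.** The section Secondary and Exploratory Outcome Measures reports the "percentage of trial participants with clinical progressive disease". A case is one in which the investigator deems that the patient will gain nothing more from the regimen and is "considering stopping it, at the time of the first radiological assessment performed as per standard-of-care". Table 1, footnote f, fixes the same moment: "at the time of the first radiological assessment performed as per standard-of-care". The two places agree with each other.

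The rest of the article bears on this as follows:

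- **Scan timing.** The Figure 2 caption has "Computed tomography scans performed approximately every two or three cycles as per standard-of-care", with cycles of 3 weeks.
- **End of involvement.** CURATE.AI Efficacy-Driven Dose Recommendations describes the end of a participant's involvement: "which is when the clinical investigator decides to cease/change the chemotherapy regimen, or until 12 months, whichever is earlier".
- **Early failures.** Study Setting and Participant Recruitment makes participants evaluable for the primary outcome measures "only if participants are able to complete the first two cycles of chemotherapy in an uninterrupted manner". It adds: "We will replace any unevaluable participants with new participants", and "we will continue to monitor and report any adverse events in the unevaluable participants".
- **Purpose.** Secondary Objective says that the incidence of clinically progressive disease will be evaluated. The Abstract, Introduction and Conclusions say that the exploratory efficacy and toxicity data will support power or sample size calculations for the RCT.
- **Status.** Table 1 gives the outcome no traffic-light threshold, and Statistical Analysis says that efficacy and toxicity outcomes will not be statistically analysed.

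**The concern.** The definition is complete as written and needs two things to be true at one moment: the participant is there to be judged, and the regimen is still running so that stopping it can be considered. Someone who died of disease in week 4, or was taken off the regimen for deterioration in week 5, satisfies neither. These are the fastest progressors, and in metastatic disease treated without curative intent, with ECOG performance status up to 2 allowed, some early failures are plausible.

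The stated objective is the incidence of progression, which includes cases before the scan. The definition captures only a landmark judgement. This is the only progression outcome that the article defines. If its rate is carried into planning the RCT, it understates how often patients fail early.

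**Working it through.** The article gives no expected progression rate, so there is no figure of its own to reproduce. The check is whether the direction of the error depends on how early failures are handled, and how large it could be.

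**Inputs from the article.** Planned n = 10 (Sample Size). First scan after about 2 to 3 cycles of 3 weeks: 2 × 3 = 6 to 3 × 3 = 9 weeks. For someone who completes two cycles (6 weeks), the time at risk of failing before the scan is therefore about 0 to 3 weeks. Failures before week 6 also meet the replacement rule.

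**Assumed inputs.** x = progressions judged at the first scan; k = disease-related deaths or stops for deterioration before it.

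**Three treatments of the k participants:**

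- scored as non-events: x/n
- dropped: x/(n − k)
- counted as events: (x + k)/n

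**Direction.** Counted minus non-event = k/n, which is positive whenever k > 0. Counted minus dropped = (x + k)/n − x/(n − k) = k(n − x − k)/[n(n − k)]. This is never negative, and is zero only if k = 0 or if everyone progresses. Both handlings therefore bias the rate downward.

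**Size, n = 10:**

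| x | k | Non-event | Dropped | Counted |
|---|---|---|---|---|
| 1 | 2 | 1/10 = 10% | 1/8 = 12.5% | 3/10 = 30% |
| 2 | 1 | 2/10 = 20% | 2/9 = 22.2% | 3/10 = 30% |
| 2 | 2 | 2/10 = 20% | 2/8 = 25% | 4/10 = 40% |
| 2 | 3 | 2/10 = 20% | 2/7 = 28.6% | 5/10 = 50% |

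Formula check for the first row: 2 × (10 − 1 − 2)/(10 × 8) = 14/80 = 17.5 points = 30% − 12.5%.

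**With replacement.** If the two early failures in the first row are replaced and neither replacement progresses, 12 people start cycle 1. Counted among all starters, the rate is 3/12 = 25%. Dropping the two gives 1/10 = 10%; keeping them as non-events gives 1/12 = 8.3%. Each missed case is then worth 1/12 = 8.3 points rather than 10.

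**Early stops that are not disease-related.** Suppose 2 of 10 stop for toxicity and 2 progress at the scan. Scoring the two stops as non-events gives 2/10 = 20%, which need not be too low. Dropping them gives 2/8 = 25%, which is higher. The downward bias does not extend to these participants.

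**Use in planning.** Assume that the RCT aims to halve the rate, with two-sided alpha 0.05, power 0.80 and 1:1 allocation (none of this is in the article). The total N is 398 at a control rate of 20%, 304 at 25% and 164 at 40%. These are the three readings of the x = 2, k = 2 row. Sampling error at n = 10 is also wide: the exact 95% interval is 2.5% to 55.6% for 2/10 and 12.2% to 73.8% for 4/10.

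**The case against.** The strongest reply is that the article is merely silent on a missing assessment, which a fuller protocol or an analysis plan would normally settle. Part of this stands. A reader might infer several things that the text does not support:

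- **That early failures count as not progressed.** No section says so. They could equally be dropped or replaced.
- **That the two-cycle evaluability rule removes them from the progression rate.** That rule is written for the primary outcome measures. The progression percentage is of trial participants.
- **That only adverse events will be known for replaced participants.** The article says that adverse-event reporting continues; it does not exclude other documentation.
- **That everyone who stops early makes the rate too low.** Stopping for toxicity or withdrawal is not progression.

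It is also fair to say that the outcome is a clinical judgement and not a radiological reading, so an investigator might record an earlier stop for deterioration as progression. In addition, a standard-of-care scan prompted by deterioration would itself be the first scan.

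What remains is a stated rule and not a gap. Both definitions place the judgement at the first scan and require the regimen to be one that the investigator is still considering stopping. Nothing in the article allows an earlier stop or a death to be recorded, so two sites could score the same patient differently. The direction of the error does not depend on which handling is later chosen.

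On weight, the objection is largely right. The outcome is exploratory, has no threshold and will not be tested, and no section names this rate as the RCT's planning parameter.

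**Conclusion.** The point holds for disease-related early failures only. Because clinical progressive disease is fixed to the first scan, those who die of disease or stop for clinical deterioration before it cannot meet the definition, and the rate is biased downward whether they are scored as non-events or dropped. The loss is k/n on the first handling (10 points per participant at n = 10) and smaller on the second. The numbers of early failures used above are assumptions; the article gives none. For participants who complete two cycles the exposed window is short, at most about 3 weeks.

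The priority is low. With about 10 participants the imprecision of the rate is as large a problem as this bias, and no progression decision hangs on it. It is worth correcting because the article intends the efficacy data to inform the RCT and the change is one of wording.

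**What to change.** In Secondary and Exploratory Outcome Measures and in Table 1, footnote f, define the outcome as any of the following, at or before the first standard-of-care scan: the investigator judges that there is no further benefit from the regimen; the regimen is stopped for clinical deterioration; or the participant dies of the disease. State the population as all participants who started cycle 1, including those later replaced or unevaluable for the primary outcome.

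Report stops before the scan for other reasons (toxicity, withdrawal, unrelated death) as a separate count of participants not assessed. Give the rate both with and without them in the denominator, so that they are not silently treated as progression-free.

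The cost is wording in two places and one extra line in the results table. No visit, test or treatment rule changes, and the treating investigator will ordinarily know the date of and reason for stopping, and of any death on treatment. The downside is a somewhat less favourable progression rate.
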